## **6.6. Rescue medication**

Rescue medication defined as drugs used to control symptoms that are induced post-vaccination could be administrated based on the investigator's contemplation. Use of rescue medication must be recorded on CRF.

## **6.7. Drug accountability**

Investigators or the designated persons such as clinical research coordinator (CRC) must maintain accurate records of dates and quantities of study product(s) received, batch/serial numbers or other identification number of each delivery, to whom given (subject-by-subject accounting), and accounts of any product accidentally or deliberately destroyed. A Drug Accountability Log must be kept current for individual subject and should contain the following information:

- ◆ The subject's identification to whom the vaccine is administrated.
- ◆ The date(s) of vaccine administrated by the subject.
- ◆ The quantity of vaccine administrated by the subject.

All the used, partially used and unused study vaccines must be retained for the study monitor to confirm the accountability data till study complete. At the conclusion of the study, all those supplies, including empty containers, must be returned to NHRI Vaccine Research and Development Center.

## **6.8. Treatment exposure and compliance**

Not applicable.

## **7. Assessment Parameters**

### **7.1. Demographics / other baseline characteristics**

The demographic and baseline characteristic data for subjects will be collected at screening (Visit 1). The demographics include date of birth, age, gender and ethnicity. Relevant history/conditions include all those present prior to the administration of study vaccine that are listed below:

- ◆ relevant medical history,
- ◆ all current medical conditions,
- ◆ allergy history,
- ◆ history of alcohol use,

Whenever possible, diagnoses but not symptoms should be recorded.

### **7.2. Immunogenicity**

The potency of EV71 vaccine ingredient, the inactivated EV71 whole virion (EV71vac bulk), will be evaluated by immunogenicity tests. Blood samples will be collected for these assessments at Visit 2 and Visit 4 prior to each vaccination and at Visit 5. These tests, including EV71 specific IgG antibody titer and EV71 virus neutralization titer, and immune epitope mapping will be conducted at NHRI.

About 7 ml of blood sample should be taken and divided into BD Vacutainer® SST™ tubes containing silica clot activator polymer and gel for immunogenicity assessments. All blood samples will be collected (without anticoagulant) and stood at room temperature for at least 10 minutes. Clotted blood samples will be centrifuged at 500 x g for 20 minutes at 4°C, and serum specimens (supernatant) will be transferred into three cryogenic vials (approximately 1000 µl/vial). After that, the blind samples labeled only with specific sample number will be delivered to NHRI under 2~8°C and stored at -80°C until processed (refer Sampling guideline in [Appendix I](#)).

#### **7.2.1. EV71 specific IgG antibody titer**

Determination of EV71 specific IgG antibody titer will be performed with enzyme-linked immunosorbent assay (ELISA). Inactivated EV71 virus was firstly coated on a 96-well microplate and stood for overnight. The microplate will be washed with PBST for one time and blocked with PBS containing 1% of BSA for 2 hours. The microplate will be washed again with PBST for 2 times. Serum specimens will be serially diluted and added into each well. The microplate will be incubated at room temperature for 2 hours and then washed with PBST for 4 times. Detection antibody (goat anti-mouse IgG-Fc antibody HRP, 1:5000) will be added into each well and followed by adding chromogenic substrate (ABST). Absorbance at 405 nm will be then measured.

#### **7.2.2. Neutralizing antibody titers**

Determination of EV71 virus neutralization titer is to determine the virus neutralization titer against EV71 virus based on the principle of TCID50 assay. Serum specimens will be serially 2-fold diluted and added into each well of the 96-well plate. 100 TCID50 of EV71

virus (E59) will be added into each well. The 96-well plate will be incubated at  $37\pm0.5^{\circ}\text{C}$  supplied with 5%  $\text{CO}_2$  gas for 4 to 6 days. Virus neutralization titer of a serum will be determined and calculated according to the formula of Reed-Muench method.

### 7.2.3. Epitope mapping

The human serum samples collected at Visit 2 and Visit 5 (baseline and 42 days after first vaccination) will be used to identify the immunodominant epitopes of EV71 virus.

The overlapping synthetic peptides of the EV71 strain TW/2086/98 VP1, VP2, VP3 and VP4 capsid proteins will be synthesized at Kelowna International Scientific, Inc. There will be a set of 57, 49, 47 and 12 overlapping synthetic peptides spanning the entire sequence of the VP1 to VP4 capsid protein, respectively. Each peptide contains 15 amino acid residues with 10 residues overlapping with the adjacent peptides.

The affinity of antibody to each synthetic peptide will be measured by ELISA. The 96-well plates (Costar) will be coated at  $4^{\circ}\text{C}$  overnight with 50  $\mu\text{l}$  of individual synthetic peptide or purified virions that will be diluted to 10  $\mu\text{g}/\text{ml}$  in coating buffer. Each well will be blocked by adding 200  $\mu\text{l}$  blocking buffer (5% non-fat milk in PBS). Human serum sample is the primary antibody which will be diluted and added 50  $\mu\text{L}$  per well to coating plate for 2 hours incubation. Shake off the antibody solution and wash 6 times with 1 x PBST for removing primary antibody. Second antibody is anti-human antibody which conjugated with HRP (Horseradish Peroxidase). Second antibody will be added 100  $\mu\text{l}$  per well and incubated for 2 hours. Shake off the antibody solution and wash 6 times with 1 x PBST for removing second antibody. The reaction will be revealed by adding TMB substrate solution (KPL) and incubates at room temperature (RT). The reaction will be stopped by adding  $\text{H}_2\text{SO}_4$  (1N) and the absorbance will be measured at 450 nm by ELISA reader.

## 7.3. Safety

### 7.3.1. Physical examination / body temperature

Complete physical examinations and oral temperature determination should be conducted by investigator at screening, Visit 2 and 4 prior to vaccination, and the last return visit (Visit 5). A complete physical will include the examination of general appearance, HEENT (head, ears, eyes, nose, throat), neck (including thyroid), lymph nodes, skin, cardiovascular, pulmonary, abdomen, neurological system and musculoskeletal/joints.

For two vaccination visits (Visit 2 and Visit 4), body temperature should be measured prior to vaccine administration. Subject with fever defined as oral temperature  $\geq 37.5^{\circ}\text{C}$  should not receive study vaccine.

Body weight will be measured in indoor clothing, but without shoes at all visits, but body height will be measured only at screening visit. Body mass index (BMI) will be calculated by taking a subject's weight in kilograms (kg) and dividing by their height in meter squared ( $\text{m}^2$ ). A subject with BMI  $> 35$  at screening should be excluded from this study.

It must be recorded when any abnormality has been found out.

### 7.3.2. Urine pregnancy test

All female subjects except those who have been surgically sterilized (defined as having undergone hysterectomy or bilateral oophorectomy or bilateral salpingectomy; tubal

ligation alone is not considered sufficient) or one year post-menopausal should receive urine pregnancy test. A pregnancy test strip will be used at screening, at Visit 2 prior to randomization and at Visit 4 prior to vaccination. Female with positive result and those who are planning to be pregnant should be withdrawn from this study.

Investigators and their delegates should instruct the females to use medically recognized method of contraception which includes intrauterine contraceptive device; oral contraceptives; diaphragm or condom in combination with contraceptive jelly, cream or foam; Norplant® or DepoProvera® until 2 months after completion of vaccination series.

### **7.3.3. Selected laboratory safety tests**

Fasting blood samples will be collected for hematological and biochemistry examinations at Visit 1, Visit 3 and Visit 5. These tests will be conducted by local laboratory in each center.

#### **7.3.3.1 Hematological examination**

The complete blood count (CBC) test includes hemoglobin (Hb), hematocrit (Hct), red blood cells (RBC) count, white blood cells (WBC) count, WBC differential and platelet counts.

Subjects with any significant hematologic abnormality at screening (Visit 1) will not be recruited into this study, and those with any significant abnormality at interim safety screening (Visit 3) should not receive 2nd vaccination.

#### **7.3.3.2 Biochemistry examinations**

Biochemistry examinations include alanine transferase (ALT), aspartate transferase (AST), γGT, alkaline phosphatase, total bilirubin, total protein, albumin, BUN, creatinine, uric acid, total cholesterol, triglyceride and fasting plasma glucose (FPG).

Subjects with any significant biochemistry abnormality at screening (Visit 1) will not be recruited into this study, and those with any significant abnormality at interim safety screening (Visit 3) should not receive 2nd vaccination. However, if the level of ALT/AST or creatinine is less than 2.5 x ULN, the test could be conducted again 1 week later and the 2nd dose of EV71 vaccine will be administrated in those with normal results after that.

### **7.3.4. Self-evaluation (solicited/unsolicited symptoms)**

A thermometer and self-evaluation diary card will be dispensed to all subjects after each vaccination. Investigators or their delegates will instruct the subjects to monitor body temperature and complete the all the assessments in the diary every evening.

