### V . Study design:

1. ☐ Control: ☐ placebo  
☐ active \_\_\_\_\_  
☐ other \_\_\_\_\_
- ☒ Uncontrolled
2. Blinding: ☒ open-label ☐ evaluator blind ☐ single blind ☐ double blind  
☐ double dummy ☐ other \_\_\_\_\_
3. Randomized: ☒ yes ☐ no
4. ☒ Parallel ☐ Cross-over ☐ Other \_\_\_\_\_
5. Duration of treatment: Two-vaccination regimen, 21 days apart
6. Titration: ☐ forced ☐ optional ☒ none
7. ☐ Multi-national ☒ Multi-center (Taiwan) ☐ Single center

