### 5.1. Visit 1 (Day -7~0) – Screening

At Visit 1, informed consent must be obtained prior to performing any procedures related to the study and after the healthy volunteer has received sufficient information about the study, the opportunity to ask any questions, and consider the options.

Subjects who have been screened should be listed on the Screening Log. Moreover, all screening procedures conducted and the primary reason for not continuing must be documented in the CRF, but no data will be entered into the database for all screened subjects who do not meet criteria for entering the study. No CRF other than the screening part should be completed for these subjects. The following study procedures will be conducted for screening assessments.

- (1) Record date of informed consent signed. Document in the subject's medical chart that he/she is participating in this study, informed consent has been obtained and a copy of the consent has been given to the subject.
- (2) Check inclusion/exclusion criteria.
- (3) Collect the demographic data, including date of birth, age, gender and ethnicity.
- (4) Collect relevant medical history and concurrent diseases. Where possible, diagnoses and not symptoms should be recorded.
- (5) Conduct a complete physical examination including the measurement of weight and height. Measure and record the oral temperature.

- (6) Collect urine samples for pregnancy test (in females of childbearing potential only).
- (7) Collect approximately 8 ml of whole blood sample for following local laboratory tests.
  - Hematological tests: CBC, including Hb, Hct, RBC count, WBC count, WBC differential and platelet count.
  - Biochemistry tests: ALT, AST,  $\gamma$ GT, alkaline phosphatase, total bilirubin, total protein, albumin, BUN, creatinine, uric acid, total cholesterol, triglyceride and glucose (fasting).
- (8) Review prior and concomitant medications. All medications, including vaccine(s), taken during the 30-day period before vaccination should be recorded.

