## 5.2. Visit 2 (Day 0) – 1st vaccination

The first dose of study vaccine should be administrated within 1 week after the screening visit. All subjects should complete the following study procedures **prior to vaccination**.

- (1) Check inclusion/exclusion criteria.
- (2) Check withdrawal criteria.
- (3) Conduct randomization of the qualified participant into one of the following dosing groups.
  - **Group A05:** 0.25 ml per dose (5  $\mu$ g total protein + adjuvant 150  $\mu$ g AlPO4)
  - **Group B10:** 0.5 ml per dose (10  $\mu$ g total protein + adjuvant 300  $\mu$ g AlPO4)
- (4) Conduct a complete physical examination with an exception of body height. Measure and record the oral temperature.
- (5) Collect urine samples for pregnancy test (in females of childbearing potential only).
- (6) Collect approximately 7 ml of whole blood sample for following central laboratory tests.
  - Immunogenicity tests: IgG and neutralizing antibody titers, and epitope mapping.

The study vaccine will be administrated intramuscularly (i.m.) in the deltoid of the non-dominant arm. **After vaccination:**

- (1) Observe closely during vaccination and at least 2 hours after vaccine administration. An appropriate medical treatment should be readily available in case of a rare anaphylactic reaction following vaccination.
- (2) Conduct a telephone follow-up 7 days after vaccine administration.
- (3) Dispense thermometer and self-evaluation diary card. Instruct the subjects to monitor body temperature and complete the diary correctly.  
Any solicited symptoms and local and/or general adverse events occurring during a 7 days post-vaccination period, and any unsolicited symptoms occurring during a 21 days post-vaccination period will be recorded on the diary card. The subjects will be instructed to contact the investigator or their delegates immediately if symptoms should manifest or in case of any signs or symptoms occurring which the subject perceives as serious.
- (4) Record concomitant medication(s)/vaccine(s) taken since the previous visit and during vaccination period.

- (5) Record and report adverse or serious adverse event if any one has occurred since the previous visit.

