#### **7.3.4.1 Solicited symptoms**

Information of solicited symptoms/AEs will be collected by the subjects in the provided diary cards during a 7-day follow-up period after each vaccination (i.e. day of vaccination and 6 subsequent days), and reported by the investigator team.

A solicited local and general symptoms or AEs are the one whose nature or intensity is consistent with the expected AEs described and listed in [Table 7-1](#).

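### No directed record of the solicited general symptoms is taken before either injection, so the absolute solicited percentages in this uncontrolled trial can include symptoms already present

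*Protocol*

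**What the plan says.** All places are in the protocol.

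- **Diary.** Section 7.3.4: "A thermometer and self-evaluation diary card will be dispensed to all subjects after each vaccination". The Visit 2 procedures (Section 5.2) put "Dispense thermometer and self-evaluation diary card" among the steps after vaccination, and the Visit 4 procedures do the same for the second card. Subjects fill it in each evening.
- **Solicited event.** Section 7.3.4.1 defines it as one "whose nature or intensity is consistent with the expected AEs described and listed in" Table 7-1, collected "during a 7-day follow-up period after each vaccination (i.e. day of vaccination and 6 subsequent days"). It sets no condition of new onset or worsening. Table 7-2 grades whatever is present from 0 to 3.
- **Baseline history.** Section 5.1: "Where possible, diagnoses and not symptoms should be recorded". Section 7.1 says much the same, "Whenever possible, diagnoses but not symptoms should be recorded", and also lists current medical conditions. The history is taken at Visit 1, up to 7 days before dose 1.
- **Before each dose.** Physical examination and oral temperature, but no scoring of the Table 7-1 symptoms.
- **Adverse event enquiry.** At Visits 2 and 4 this too is listed after vaccination, and Section 7.3.5 makes the questioning non-directive.
- **Minor illness.** A note in Section 4.3.2 allows vaccination during minor illness and gives diarrhea as an example. Diarrhea is a solicited general symptom in Table 7-1.
- **Endpoint and design.** The percentage, intensity and relationship of local and systemic symptoms is a primary endpoint (Section 9.1). Section 10.3.2 tabulates it with a 95% confidence interval by dose and overall. The synopsis marks the design as "Uncontrolled".

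**The concern.** Apart from fever, which is measured before each dose, the general symptoms in Table 7-1 are mostly things people feel from time to time without a vaccine: nausea, appetite loss, headache, myalgia, joint pain, fatigue, shivering. In a controlled trial the background rate shows up in the control arm. Here there is none, so the subject's own state just before the injection is the nearest available reference, and it is not recorded in any directed way.

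A symptom present at injection and still present that evening meets the solicited definition as written. The note on minor illness shows that the protocol itself foresees such a subject at dose 2. What is at stake is the absolute reactogenicity percentage for each dose, which is what this phase I trial sets out to report, and the quality of the information behind the causality rating.

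**Working it through.** The protocol states no background rate and Section 10.6 gives no sample size calculation, so there is no stated figure to reproduce. The check has two parts.

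**1. Could any existing step supply the missing record?**

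| Step | What it gives | What it leaves open |
|---|---|---|
| Examination and temperature before each dose | Fever, physical signs | No score for headache, fatigue, myalgia or nausea |
| History at Visit 1 | Diagnoses, current conditions; symptoms where no diagnosis is possible | Up to 7 days before dose 1; not repeated before dose 2 |
| Adverse events since the previous visit (Visits 2 and 4) | Events the subject mentions | Asked after the injection, non-directively; the Table 5-1 adverse event row starts only at Visit 2 |
| Adverse events at Visit 3 | Events between Day 0 and Days 14-17 | Not the state at dose 2 |
| Unsolicited collection after dose 1 | Days 0-20 | Defined as events not matching the solicited list, so a headache on Days 7-20 fits poorly; dose 2 falls on Days 21-24 |
| Onset date and causality rating | A route to classing an event as unlikely or unrelated | Relies on recall and on the investigator asking, in an open-label trial |

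Several steps help. None records the Table 7-1 symptoms before a dose.

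**2. How large could the effect be?**

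Inputs: 30 subjects per group, from Table 6-1 (A05: 1 + 1 + 3 + 25 = 30; B10: 1 + 4 + 25 = 30). All rates below are assumptions. Let *b* be the share with at least one listed general symptom before the injection and *t* the share who truly react. Take the two as independent, and take every pre-dose symptom as lasting to the evening diary.

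Reported share = 1 − (1 − *t*)(1 − *b*), so the excess is *b*(1 − *t*).

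| *b* | *t* = 20% | *t* = 30% | *t* = 40% |
|---|---|---|---|
| 5% | 4.0 points | 3.5 | 3.0 |
| 10% | 8.0 | 7.0 | 6.0 |
| 20% | 16.0 | 14.0 | 12.0 |

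Example: *t* = 30% and *b* = 10% give 1 − 0.7 × 0.9 = 37%. Times 30, the range of 3.0 to 16.0 points is 0.9 to 4.8 subjects per group.

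The chance that a group contains at least one such subject at a given injection is 1 − (1 − *b*)^30, which is 79%, 96% and 99.9% for *b* = 5%, 10% and 20%.

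If only a fraction of pre-dose symptoms lasts to the evening, the excess shrinks in proportion, so for these rates the table is an upper bound.

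**Between doses.** With the same *b* in both groups, the reported difference is (*t*_B10 − *t*_A05)(1 − *b*). A true 40% against 20% would read as 19 points at *b* = 5% and 16 points at *b* = 20%, instead of 20. The direction is kept and the difference is somewhat diluted.

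**Scale.** The exact 95% interval for 3 of 30 is 2.1% to 26.5%. The possible excess is modest beside that sampling error, but it acts in one direction and the interval does not account for it.

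**The case against.** The strongest reply is that counting every symptom and reporting causality separately is a defensible, conservative choice for a phase I safety study. Relationship to vaccination is part of the primary endpoint. The investigator must rate it for every solicited event (Section 7.3.5.2), with unlikely and unrelated available, and onset dates are required (Section 7.3.5). Current conditions and concomitant medication are recorded, subjects must be free of obvious health problems, fever bars either dose, and moderate or severe illness is a contraindication to dose 2. How to treat an onset before injection is a derivation that may sit in a statistical analysis plan that is not shown.

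Much of this stands, and it rules out stronger readings. A reader might infer that any pre-existing headache is counted as a vaccine reaction. The documents do not support that: it can enter the raw solicited percentage, but it may still be rated unrelated. A reader might also infer that the history forbids recording symptoms. Both instructions are qualified by possibility, so an undiagnosed symptom can be noted. Nor is the gap shown to be equal at both doses, since dose 2 is preceded by follow-up from dose 1. The absence of a counting rule is not a fault in itself.

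What does not fall away is the data collection. Visit procedures and diary timing are fixed in the protocol, and no later analysis rule can use a pre-dose score that was never taken. The remedy also has limits: a single score cannot identify unrelated symptoms that begin on Days 1-6, so it does not replace a control group.

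**Conclusion.** The point holds as a minor weakness in data collection. The protocol takes no directed record of the Table 7-1 general symptoms before either injection, and its solicited definition does not ask for new onset or worsening. The absolute solicited percentages can therefore include symptoms already present. Onset dates and the causality rating reduce this without removing it, and the comparison between doses is little affected.

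The true size is unknown. The upper bound of about 3-16 points (roughly 1 to 5 of 30 subjects) rests wholly on assumed pre-dose prevalences of 5-20%, true rates of 20-40%, independence and full persistence to the evening diary. Nothing in the documents supports the upper end for screened healthy volunteers. The note on minor illness is cited only because it shows the situation is foreseen; whether to vaccinate in that case is not questioned here.

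**What to change.** - At Visits 2 and 4, alongside the existing pre-vaccination examination, have the subject score the Table 7-1 general symptoms once on the Table 7-2 scale before the injection. At Visit 4 add the injection site, since Section 6.4 names the same arm for both doses.
- Keep the all-events solicited percentage as the main count. Add one supplementary table of events that were absent before the injection or of higher grade afterwards.
- Give the pre-dose score to the investigator for the causality rating.

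The new-or-worse count should stay supplementary because it can hide a real reaction: mild fatigue before the dose that clears and returns at the same grade on Day 3 would drop out of it.

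The cost is a couple of minutes at two existing visits and one extra table. The sample size does not change.
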